### Estimation of the cumulative ambient UV-B irradiation

We calculate the ultraviolet-B (UV-B) radiation flux density as detailed below, using a radiative-transfer code called ‘SMARTS2 (Simple Model of the Atmospheric Radiative Transfer of Sunshine, version 2)’ developed by Gueymard to calculate the flux density of solar radiation on the ground surface *E(λ)* for wavelength region between 280 and 4,000 nm [28], based on which we estimate the cumulative ambient UV-B irradiation from 1 month to 1day before blood drawn.

In particular, for wavelengths from 280 to 1,700 nm, calculations can be made at 1 nm intervals. UV spectrum of wavelength *λ* at the horizontal plane surface is expressed as follows;

$$E(\lambda )=E_{bn}(\lambda )\;\cos\;\theta_{z}+I_{d}(\lambda )$$

where

*E* (*λ*): UV flux density of the wavelength, *λ*,

*E*_*bn*_ (*λ*): UV spectrum of the direct component of solar radiation,

*θ*_*z*_: solar zenith angle,

*I*_*d*_ (*λ*): UV spectrum of the diffusive component of solar radiation.

This equation allows us to calculate the UV spectrum *E*_*bn*_ (*λ*) and *I*_*d*_ (*λ*) at the ground surface for a given season, time, and place under a cloudless sky. We apply this calculation to the sites where subjects are recruited at each participating university or college in the study. The UV flux reaching the top of the atmosphere from the sun is corrected for the distance between the earth and the sun for each day of the year. Total ozone at each site is given by measurements of NASA’s OMI [29] and OMPS [30] satellites which have been reporting the ozone total column data on a regular basis. The optical thickness of aerosols is observed under a cloudless sky at the Tsukuba station, Japan Meteorological Agency, using a sun-photometer that split the direct solar radiation into 368, 500, 675, 778, and 862 nm portions, which yield the Angstrom parameters, *α* and *β*. The data for aerosols for Tsukuba is used when there are no data available for aerosols at study sites. Rayleigh scattering is related to the number of air molecules that may generate atmospheric pressure. UV spectra have been observed by the Japan Meteorological Agency, every hour on a daily basis with Brewer spectra available for every 0.5 nm interval [31].

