## Results and discussion

We plan to register 150 cases each in the summer and winter quarters of 2021–2022. Case registration has been delayed due to the spread of coronaviruses, and 115 cases were collected from 6 institutions by March 2021. We plan to conduct an interim analysis when the number of registered cases reaches 200 or more, and we plan to complete case registration and conduct the final analysis by around September 2022.

The purpose of this study is to determine how serum 25(OH)D concentration in young women is affected by such factors as latitude, season, diet, and lifestyle, and build a prediction model to predict serum 25(OH)D concentrations. The results of this study may provide a scientific basis for the forthcoming Dietary Reference Intakes and other various guidelines. We also plan to develop a tool to screen the risk of VDD and make it available through our website so that individuals can monitor their vitamin D status and easily assess their risk of vitamin D deficiency or insufficiency, which will lead to the prevention of lifestyle-related diseases by improving VDD.

This study is characterized by collecting data on UV-B exposure and lifestyle habits from four different latitudes (seven sites). Although previous reports are available in Japan on the circulating 25(OH)D levels at different latitudes [10,11], they suffer from the narrow range of latitudes [11], and lack of data on UV-B exposure. Another previous study conducted in Hokkaido (43°N) and Kumamoto (33°N) revealed a strong association between latitude and lifestyle [19]. Against this background, we will clarify how latitude and lifestyle affect UV exposure in this study.

There have been some previous papers reporting serum 25(OH)D concentrations in summer and winter, which has yielded conflicting results such as a significant correlation of serum 25(OH)D with UV exposure time and UV energy only in summer [19,20], and significant prediction of 25(OH)D level by UV index but with opposite direction of the association according to the blood collection period [12]. Then, the present study including the determination of serum 25(OH)D concentrations both in summer and winter at different UV irradiance levels together with various demographic variables would be of help clarifying the relationship between ambient UV-B irradiation and serum 25(OH)D levels on a seasonal basis.

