A previous study has reported that the use of sunscreens and sun protection tools did not affect serum 25(OH)D concentrations in multivariate regression models [19]. This paper, however, included both sexes, which can be a confounding variable, and reports on the effect of the use of sunscreens and sun protection tools on serum 25(OH)D concentrations are quite limited in young women except in pregnant women [11]. Then, the study design of the present study including only women can rather be a strength, and suited for clarifying the effect of use of sunscreen and sun protection tools reduce serum 25(OH)D concentrations.

Individual UV irradiation dose can be evaluated either by direct measurement or estimation. As the former, the use of wearable devices is useful enabling a more accurate assessment of individual UV doses, which, however, is a burden to the participants. Then, we have not adopted such devices, and estimate the UV exposure for each region. The association of estimated UV irradiation dose and serum 25(OH)D levels has previously been reported [12,13]. For example, Cardoso et al [12] used the UV index obtained from the Portuguese Institute of Oceanography and Atmospheric Research. O’Sullivan et al. estimated the cumulative and weighted daily ambient dose of UV-B at wavelengths where vitamin D synthesis is possible [13].

Much more strong association between the dietary vitamin D intake and serum 25(OH)D levels could be expected than that in European and American studies, with the possible bases described below. Previous European reports on the ultraviolet effects on vitamin D status had a methodological flaw; no data on dietary vitamin D intake [12,13]. Another important issue to be considered is the markedly different prevalence of subjects under vitamin D supplementation between Europe and Japan. It was as high as 49.9% in the European study [13], whereas it was only 5.1% in a Japanese study for pregnant women with an age distribution similar to that in our study [11]. In the above-mentioned European studies, it is quite likely that the overwhelming effects of supplementation have obscured the contribution of dietary vitamin D. In Japan with a much lower percentage of vitamin D supplementation, a strong association between dietary vitamin D intake and serum vitamin D concentration could be expected, unlike the results from European and American studies.

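### The one-month ambient UV-B index is computed for a cloudless sky with no stated cloud correction, which distorts the UV-B coefficient and its reading by season

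*Protocol article*

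**What the plan says.** All of the method stands in the protocol article, section on estimation of the cumulative ambient UV-B irradiation.

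- **Condition.** The radiative-transfer equation yields the direct and diffuse UV spectrum "at the ground surface for a given season, time, and place under a cloudless sky".
- **Where it is used.** "We apply this calculation to the sites where subjects are recruited at each participating university or college in the study".
- **Window.** On this basis, "we estimate the cumulative ambient UV-B irradiation from 1 month to 1day before blood drawn".
- **Inputs named.** Sun–earth distance, satellite total ozone per site, aerosol optical thickness and Rayleigh scattering. The aerosol data are themselves cloudless-sky observations from one station: "The data for aerosols for Tsukuba is used when there are no data available for aerosols at study sites".
- **Observed UV.** The section closes with "UV spectra have been observed by the Japan Meteorological Agency, every hour on a daily basis with Brewer spectra available for every 0.5 nm interval". It does not say whether these spectra correct, validate or replace the calculated values.

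The statistical analysis section lists the index as one candidate predictor, beside residential area and season of blood collection. Regression coefficients are to be reported with 95% confidence intervals and Wald p-values. The results and discussion section presents UV-B data as a distinguishing feature of the study and expects it to help in "clarifying the relationship between ambient UV-B irradiation and serum 25(OH)D levels on a seasonal basis". The stated limitations do not mention cloud.

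**The concern.** A month of cloudless-sky flux is an upper bound on what reached the ground. If the sky were equally cloudy everywhere and always, the index would only be on the wrong scale, and neither tests nor predictions would change. Cloud differs by place and season, however, and place and season are the contrasts along which this index varies. The omitted factor is therefore tied to site and season and is not random noise between women.

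What is at stake is the meaning of the UV-B coefficient. A difference between the summer and winter associations could reflect different average cloud rather than a different biological relationship. Within early summer, when the clear-sky difference between latitudes is small, the index could even rank sites in the wrong order.

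**Working it through.** The document gives no UV-B value, cloud factor or error size, so there is no stated figure to reproduce. What follows is illustration under named assumptions.

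**1. How large is the clear-sky contrast?** Assumed proxy for daily clear-sky UV-B: the integral over the day of cos(zenith)^k, with k from 2 to 3. It leaves out ozone and aerosol. The latitudes 43°N and 33°N are those the discussion gives for a previous study in Hokkaido and Kumamoto; this study's own latitudes are in Fig 1, which is not shown. The last column gives the southern site a 10% lower cloud transmission (assumed), i.e. the ratio × 0.9.

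| Mid-month | 33°N / 43°N, k = 2 to 3 | × 0.9 |
|---|---|---|
| June | 1.04–1.09 | 0.94–0.98 |
| July | 1.06–1.11 | 0.95–1.00 |
| August | 1.13–1.23 | 1.02–1.11 |
| September | 1.28–1.45 | 1.15–1.31 |
| January | 1.97–2.64 | 1.77–2.38 |

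In June and July a 10% transmission difference cancels or reverses the ranking. From August on, and in winter, it does not. If monthly transmission ranged from 0.6 to 0.9 across sites (assumed), the relative distortion could reach 0.9/0.6 = 1.5, more than the September contrast but less than the January one.

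**2. What happens to a season-specific slope?** Let the true model be Y = a + βU, with ambient U = T × C, where C is the clear-sky value and T the transmission. If T is the same at all sites within a season, regressing Y on C gives slope βT. With T = 0.6 in one season and 0.9 in the other (assumed), the slopes are 0.6β and 0.9β. That is an apparent 1.5-fold seasonal difference where the true slope is the same.

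**3. What happens to a common slope and to prediction?** Simulation: n = 600 × 0.70 = 420; assumed latitudes 43, 36, 34.5 and 33°N; summer and winter; k = 2.4; transmission drawn independently and uniformly for each region-season cell; 400 data sets per range; linear regression without and with region and season terms.

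| Transmission | Midpoint | Slope as share of true, without / with region and season | R², true UV-B → clear-sky, without | R², with |
|---|---|---|---|---|
| 0.8–0.9 | 0.85 | 0.86 / 0.86 | 0.396 → 0.395 | 0.402 → 0.402 |
| 0.7–0.9 | 0.80 | 0.80 / 0.80 | 0.391 → 0.387 | 0.397 → 0.395 |
| 0.6–0.9 | 0.75 | 0.75 / 0.75 | 0.394 → 0.382 | 0.399 → 0.393 |
| 0.5–0.9 | 0.70 | 0.70 / 0.69 | 0.392 → 0.368 | 0.398 → 0.385 |

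Two readings follow. First, the average shrinkage tracks the midpoint of the range, so on average it is a scale change. The site-and-season part shows as extra spread: without region and season, the SD of the slope relative to its mean is 0.062/1.003 = 6% with no cloud and 0.084/0.697 = 12% at the widest range. Second, R² falls by at most 0.392 − 0.368 = 0.024. The simulation draws cloud independently of season and fits one slope for both, so it does not show the seasonal effect in step 2.

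**The case against.** Five points can be made for the plan.

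- **The article condenses a fuller protocol, and the observed spectra may be the correction.** It is true that correction is not shown to be absent. But the section is not silent: it names the inputs, states the cloudless condition and says that this calculation is applied to the sites. A reader following it would produce an uncorrected index. The sentence "UV spectra have been observed by the Japan Meteorological Agency, every hour on a daily basis" gives the observations no task.
- **The main product is a prediction model.** This stands. UV-B is one of many candidates, region and season can absorb part of the error, and the loss of R² in the illustration is small. The harm is to the coefficient and its seasonal reading, which the discussion also sets as an aim.
- **The figures are assumed.** This also stands. The proxy omits the site-specific ozone that the plan does use, the latitude pair comes from a cited study, and the transmission values are not in the document. Mid-July alone would overstate the case, because draws run to September.
- **Area-level estimation was a deliberate choice to spare participants wearable devices.** That is reasonable, but a cloud factor is also area-level and adds no burden.
- **A nearest-station factor has error of its own.** True, and a reason to keep both versions.

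A reader might also infer that the spectrum is used without weighting for vitamin D synthesis, since the discussion credits a cited study with a "cumulative and weighted daily ambient dose of UV-B at wavelengths where vitamin D synthesis is possible". The document does not say how this study sums over wavelength. That inference rests on silence, is unrelated to cloud, and is not part of this point.

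**Conclusion.** The point holds in a limited form. As described, the index measures potential UV-B while being named and interpreted as ambient UV-B, and the omitted cloud factor varies with site and season. This can distort the UV-B coefficient and above all a comparison of that coefficient between summer and winter.

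The size is conditional. With the cos(zenith) proxy, an assumed 10% transmission difference matches the 33°N/43°N contrast in June–July only; with an assumed transmission range of 0.6 to 0.9, site or season distortion reaches 1.5-fold. The true error cannot be computed from the document.

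Two stronger readings are not supported. The text does not establish that no cloud correction will be made, only that none is stated. Nor does the omission invalidate the screening model, whose accuracy probably suffers little. The change is worth making before the final analysis because the affected aim is stated and the repair is cheap.

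**What to change.** For each site and day, multiply the clear-sky UV-B by a cloud factor, then sum over the month before the draw: index = Σ (clear-sky UV-B on day d × factor on day d). The factor is observed UV, or observed surface solar radiation, at the nearest meteorological station, divided by the calculated clear-sky value for the same quantity at that station. Name the station used for each site.

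Keep the uncorrected clear-sky index as a sensitivity analysis, so that a reader can see whether the UV-B coefficient and its seasonal difference depend on the correction. State in one sentence what the hourly observed spectra are used for. If no correction is made, call the index potential UV-B and list the cloudless-sky assumption among the limitations.

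The cost is desk work on routine meteorological data, which can be done after collection and adds no burden for participants. The downside is that the nearest station is not the campus, so the factor carries its own error.

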### Statistical analysis

The continuous variable will be expressed as mean ± standard deviation or median (interquartile range), and a categorical variable as frequency (percentage). Mann-Whitney U test and Kruskal-Wallis test will be used for the comparison between two groups and more than two groups, respectively. The chi-squared test will be used for categorical data.

An interim summary will be performed when the number of registered cases exceeds 200. The data will be summarized by region and institution. The inclusion criteria for analysis will be reviewed. We will also check for missing values and outliers. Predictors and prediction models will be determined in the final analysis when all cases have been collected.

Multivariate linear and logistic regression models are used to determine the predictors and predictive models for serum 25(OH)D concentration and VDD as outcomes, respectively. The regression coefficients and odds ratios will be calculated, and their 95% confidence intervals and p-values by Wald test will be calculated. Candidate predictors include age, residential area, skin type, smoking status, medication history, habitual drinking, physical activity, the season of blood collection, habitual sun exposure time and frequency, sunscreen use, the experience of suntan within the past 12 months, vitamin D supplement use, the habitual avoidance of sun exposure with parasol use or wearing long sleeve clothes, weekly frequency of vitamin D abundant fish consumption, and cumulative ambient UV-B irradiation.

Two-thirds of the randomly selected data will be used to build the predictive model, and the remaining data will be used to validate the built model. In the test set, variables shown to be significant in the univariate analysis and previously reported predictors are inserted into the multivariate model to construct the predictive model. In the validation set, the predictive performance of the prediction model is checked with the degrees of freedom-adjusted R-squared or AIC for linear regression analysis, and with the c-index for logistic regression analysis. In addition, as model calibration, the predicted and observed values are compared using Cook’s D for linear regression analysis and Hosmer-Lemeshow test for logistic regression analysis. Reporting on the construction of the predictive model will be done following the TRIPOD statement [32].

Statistical significance will be set at a two-tailed p-value < 0.05 for all analyses. All statistical analyses will be performed according to the statistical analysis plan decided before the analysis.

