### Planned size

The sample size required for this study was calculated to be 600 cases; based on a previous study showing that 52% of females aged 17–18 years had VDD (serum 25(OH)D level below 20 ng/mL) [8], and assuming that the proportion of VDDs is also 50% in the study population, we expect 300 individuals to have VDDs. Finally, we expect 30% of the subjects to drop out of the study due to incomplete data sets and withdrawal of consent.

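### Wald inference is named for the VDD logistic model; if supplement use is rare and strongly protective, its p-value and confidence interval can fail where a likelihood-based method would not

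*Protocol article*

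**What the plan says.** The Statistical analysis section of the protocol article plans multivariable linear regression for serum 25(OH)D and logistic regression for VDD. For the resulting coefficients and odds ratios, "their 95% confidence intervals and p-values by Wald test will be calculated". Strictly, the Wald test is tied to the p-values; Wald confidence intervals are the natural reading, though not the only one. No likelihood-ratio, profile-likelihood, exact or penalised alternative is mentioned.

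The same section lists vitamin D supplement use among the candidate predictors and builds the model on a random two-thirds of the data. Two-sided p < 0.05 applies to all analyses.

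Planned size states that "The sample size required for this study was calculated to be 600 cases", "assuming that the proportion of VDDs is also 50% in the study population", and that "we expect 30% of the subjects to drop out of the study due to incomplete data sets and withdrawal of consent".

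On supplement use, Results and discussion contrasts 49.9% in a European study with Japan, "whereas it was only 5.1% in a Japanese study for pregnant women with an age distribution similar to that in our study". Of the European studies it says that "it is quite likely that the overwhelming effects of supplementation have obscured the contribution of dietary vitamin D".

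**The concern.** The Wald test in logistic regression is unreliable for a binary predictor that is both rare and strong. As the effect grows, the cell of VDD cases among the exposed empties. The standard error then rises faster than the coefficient, and the test statistic falls back towards zero. With no VDD case among users, the estimated odds ratio goes to 0, the standard error is arbitrarily large and the Wald p-value is close to 1, although the likelihood shows a clear association.

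Supplement use may be such a predictor here. It is something a woman can change, and it is a candidate input to the planned screening tool. The logistic table could report it as non-significant with an unusable interval when the data point strongly the other way.

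**Working it through.** **Inputs from the protocol article.** Planned size: 600 women, 50% VDD, 30% loss. Statistical analysis: two-thirds of the data for building, Wald test, two-sided 0.05. Results and discussion: 5.1% supplement use in a cited study of pregnant women.

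**Inputs not in the document (assumed).** That 5.1% applies to this sample, with 3% to 10% as a range. That 5%, 10% or 20% of users have VDD. VDD in non-users is set at the planned 50%.

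**The plan's own figure.** 600 x 0.50 = 300 expected VDD cases, as stated.

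**Users in the building set.**
- 600 x (1 - 0.30) = 420; 420 x 2/3 = 280; 280 x 0.051 = 14.3, about 14 users and 266 non-users.
- At 3% use: 280 x 0.03 = 8.4, about 8. At 10%: 28.
- If 600 is read as the number left after losses: 600 x 2/3 = 400; 400 x 0.051 = 20.4, about 20.

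**Chance that no user has VDD, (1 - p)^n.**
- 14 users: 0.80^14 = 4%; 0.90^14 = 23%; 0.95^14 = 49%.
- 20 users: 1%, 12% and 36% at the same rates.
- At p = 10%: 43% with 8 users and 5% with 28.

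**What each test gives, 14 users against 133/266 non-users with VDD.** Wald: log OR = ln(ad/bc), SE = sqrt(1/a + 1/b + 1/c + 1/d). Likelihood ratio: twice the log-likelihood difference, on 1 df.
- 0/14: fitted SE about 13,000, Wald p = 0.999. Likelihood ratio: 266 ln 0.5 = -184.38 with separate rates, 133 ln 0.475 + 147 ln 0.525 = -193.73 with a common rate; 2 x 9.35 = 18.7, p = 0.000015.
- 1/14: OR = 1/13 = 0.077, SE = sqrt(1 + 1/13 + 2/133) = 1.045, Wald 95% CI 0.010 to 0.596, p = 0.014. Likelihood ratio p = 0.0006.
- 3/14: Wald p = 0.050; likelihood ratio p = 0.031.

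**Power, exact enumeration of the 2x2 table, 14 users and 266 non-users.**

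| VDD in users | OR against 50% | Non-user VDD count random: Wald / LR | Non-user count fixed at 133: Wald / LR |
|---|---|---|---|
| 20% | 0.25 | 54% / 66% | 65% / 70% |
| 10% | 0.11 | 67% / 94% | 73% / 96% |
| 5% | 0.05 | 49% / 99% | 51% / 99.6% |

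Wald power drops between OR 0.11 and OR 0.05 while likelihood-ratio power rises. With 20 users and the non-user count fixed, power is 87% against 99% at a 10% VDD rate and 64% against 100% at 5%. With the number of users also left random (5,000 simulated sets of 280), the likelihood-ratio test is significant and Wald is not in 15%, 31% and 53% of sets at 20%, 10% and 5%.

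**With covariates.** A simulation with 280 women, 8 other covariates and VDD of 30% in summer and 70% in winter (assumed) gave Wald against penalised likelihood-ratio power of 57% / 65% at OR 0.2, 71% / 89% at OR 0.1 and 60% / 97% at OR 0.05. The penalised test's type I error was 5.2%.

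**The case against.** Several stronger readings are tempting, and the document does not support them.

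- **That the plan itself predicts about 14 users.** It does not. The 5.1% is a cited rate in pregnant women, used to argue about dietary intake. The participants are undergraduate nutrition students, whose rate may differ.
- **That the plan expects a very strong effect in the individual user.** The phrase about overwhelming effects concerns a sample in which 49.9% took supplements, so that the contribution of diet was masked. It gives no odds ratio, and no figure in the article supports one near 0.1 or below.
- **That supplement use would be lost at the univariate step.** Wald is tied to the multivariable models. The only test the section lists for categorical data is the chi-squared test, which at 0/14 against 133/266 gives p = 0.0003. Previously reported predictors enter the model in any case.
- **That other uncommon levels, such as extreme skin types or current smoking, fail in the same way.** No frequencies are given, and the failure needs a strong effect as well as a rare level.
- **That the loss of power is due to the test alone.** At an odds ratio of 0.25 or weaker, it comes mainly from having so few users.

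It is also fair to say that Wald is a conventional default, that an exploding standard error is easy to see in the output, and that the analysis plan, which is not shown, could contain a fallback. The c-index does not use the Wald p-value, and the linear model for 25(OH)D still estimates the supplement effect.

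These points narrow the concern without removing it. The article names a specific test; this is not a detail left open. For a rare, strong predictor, that test is clearly worse than an alternative available at almost no cost.

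**Conclusion.** The concern holds in limited form. It is conditional on two assumptions that the document does not settle: supplement use near 5% (about 14 users, with 8 to 28 as a range) and VDD in only about 5% to 10% of users. Under both, Wald inference gives up roughly 27 to 50 percentage points of power (94 - 67 and 99 - 49), and in 23% to 49% of samples it leaves no usable interval. If 20% of users have VDD, the difference is about 5 to 12 points. What is at risk is the p-value and confidence interval for a rare, strong predictor in the VDD logistic table. Predictor entry, the c-index and the linear model are not shown to be harmed. The change is worth making before the final analysis because it costs so little.

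**What to change.** For the logistic models, replace the Wald test with likelihood-ratio p-values and profile-likelihood 95% confidence intervals. Where a predictor level has an empty or nearly empty outcome cell, report Firth-penalised estimates with profile penalised-likelihood intervals. An ordinary likelihood-ratio test already recovers the power, so penalisation throughout is unnecessary. It is needed in the empty-cell case because the unpenalised odds ratio is then not finite on the log scale. The linear model can stay as it is.

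The cost is a sentence or two in the analysis section, a standard software option and a little more analysis work. The penalised odds ratios are pulled slightly towards 1. No extra data are needed.

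### The single random two-thirds/one-third split is valid but inefficient for this sample; build on all data and validate by bootstrap

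*Protocol article*

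**What the plan says.** The Statistical analysis section of the protocol article sets the validation design itself: "Two-thirds of the randomly selected data will be used to build the predictive model". The other third is held back as the check on that model. In the building part (which the article calls the test set), "variables shown to be significant in the univariate analysis and previously reported predictors are inserted into the multivariate model". Performance in the remaining third is judged by adjusted R-squared or AIC for the linear model and by the c-index for the logistic model. The article nowhere adds resampling, cross-validation or a split by site, region or season. Its commitment to TRIPOD concerns reporting and leaves the design as it is.

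The Planned size section gives the numbers to be split: "The sample size required for this study was calculated to be 600 cases", "assuming that the proportion of VDDs is also 50% in the study population", and "we expect 30% of the subjects to drop out of the study due to incomplete data sets and withdrawal of consent". The Results and discussion section announces a public website tool for screening the risk of vitamin D deficiency (VDD), and describes data from four latitudes and seven sites.

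**The concern.** A single random split pays twice. The model is fitted to two-thirds of the women, so its coefficients are noisier and more overfitted than the data require. Its performance is then measured in only one-third, so the reported c-index is imprecise and would change with another random draw. Both costs grow when there are many candidate parameters per VDD case, as is likely here: 15 items are named as candidates, and many have several categories in Table 1.

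A separate matter is what the check can show. A randomly chosen third comes from the same institutions, seasons and student population as the other two-thirds. UV-B is calculated for the recruiting sites, so it varies only by site and blood-draw date. The check therefore does not speak to a user at a new site or latitude.

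**Working it through.** **Inputs from the article.** Planned number 600; VDD prevalence 50%; loss 30%; split 2:1; selection by univariate significance plus previously reported predictors.

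**Assumptions, not in the article.** True c-index 0.65 to 0.80; number of parameters; effect sizes. The 15 named items give about 16 parameters if each scale is one term, and about 45 if the Table 1 categories become indicator variables.

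**The plan's own figure.** 600 × 0.50 = 300, which agrees with "we expect 300 individuals to have VDDs". The 600 itself cannot be derived, because no precision or events-per-parameter target is given. Nor does the Planned size section say whether 600 stands before or after the 30% loss, so both cases are carried.

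**Split sizes.**
- Loss taken from 600: 600 × 0.70 = 420. Build 420 × 2/3 = 280 (140 with VDD); validate 140 (70 with VDD).
- 600 analysable: build 400 (200 with VDD); validate 200 (100 with VDD).

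**VDD cases per candidate parameter.**
- With 420: 140/16 = 8.8 and 140/45 = 3.1 under the split; 210/16 = 13.1 and 210/45 = 4.7 on all data.
- With 600: 200/16 = 12.5 and 200/45 = 4.4 under the split; 300/16 = 18.8 and 300/45 = 6.7 on all data.

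**Precision of the validation c-index (Hanley–McNeil).** With c the c-index, n women with VDD and n without, Q₁ = c/(2−c) and Q₂ = 2c²/(1+c):

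SE² = [c(1−c) + (n−1)(Q₁−c²) + (n−1)(Q₂−c²)] / n²

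At c = 0.75: Q₁ = 0.6000, Q₂ = 0.6429, c² = 0.5625.
- n = 70: [0.1875 + 69 × 0.0375 + 69 × 0.0804] / 4900 = 0.00170; SE 0.041; 95% half-width 0.081 (0.67 to 0.83).
- n = 100: [0.1875 + 99 × 0.0375 + 99 × 0.0804] / 10,000 = 0.00119; SE 0.034; half-width 0.067 (0.68 to 0.82).

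Across true c-indices from 0.65 to 0.80 the half-width runs from 0.091 to 0.074 with 140 women, and from 0.076 to 0.061 with 200.

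**Precision of R-squared.** With SE = √[4R²(1−R²)²/n] and R² = 0.30, the half-width is 1.96 × √(4 × 0.30 × 0.49/140) = 0.127 with 140 women and 0.106 with 200.

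**Split against all data with bootstrap (simulation, 50% prevalence, 8 real predictors).** Each pair gives the split first, then all data. True c and slope are those of the fitted model in a large independent population. RMSE is that of the estimated c-index.

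| Scenario | True c | Calibration slope | RMSE |
|---|---|---|---|
| 420 women, 43 parameters, all forced in, log OR 0.4 per SD | 0.696, 0.716 | 0.43, 0.57 | 0.040, 0.031 |
| 420 women, 43 parameters, univariate p<0.05, log OR 0.4 per SD | 0.717, 0.742 | 0.70, 0.82 | – |
| 420 women, 30 parameters, all forced in, log OR 0.33 per SD | 0.674, 0.689 | 0.50, 0.62 | 0.045, 0.032 |
| 600 women, 30 parameters, all forced in, log OR 0.33 per SD | 0.688, 0.698 | 0.61, 0.71 | 0.036, 0.023 |

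With 16 parameters the slopes were 0.78 and 0.85. Over 16 to 43 parameters at log OR 0.4, with and without selection, at 420 and 600 women, using all data adds about 0.01 to 0.03 to true c and about 0.05 to 0.14 to the slope. RMSE falls from about 0.035–0.046 to 0.022–0.032. With 100 to 200 simulated data sets per reported scenario, these figures are approximate.

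**The case against.** The best defence is that a random split is a legitimate method whose estimate is almost free of bias: in the 30-parameter simulation it was off by +0.004 (420 women) and +0.002 (600), against +0.014 and +0.008 for the bootstrap. That stands. The case against the split is one of efficiency, and the bootstrap's lower variance outweighs its bias.

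Several stronger readings are tempting and should be resisted.

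- A reader might take slopes of 0.43 and 0.57 as what the plan would deliver. They arise only when all 43 parameters are forced in. The article selects on univariate significance and adds previously reported predictors, whose number it does not give, so the truth lies between the forced and the selected scenarios.
- A reader might blame the split for the poor slope. In the forced 43-parameter case, moving from 280 to 420 women adds 0.14, while ridge shrinkage adds a further 0.27 (0.57 to 0.84). Most of the deficit is overfitting.
- A reader might set 0.081 against the Hanley–McNeil half-width of 0.046 for 420 women. That figure treats all 420 as independent validation data, which they are not under the bootstrap. The RMSE comparison is the fair one.
- A reader might infer that the published equation must ignore a third of the women. The article neither states nor excludes a refit on all data. A refit would recover the loss in the model, but not the precision of the check.
- A reader might think the bootstrap cures the same-sites limitation. It does not; it resamples the same sites and seasons.

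The article already cautions about generalising beyond young women and about selection bias among nutrition students. It does not discuss performance at a site that was not sampled.

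**Conclusion.** The concern holds as a recommendation on efficiency, with high confidence in its direction and less in its size. The article itself chooses a single random split. The choice is valid, but it leaves 280/140 or 400/200 women, a c-index known to within about ±0.08 or ±0.07, and a result tied to one draw. Modelling on all data with bootstrap validation was better in both readings of the sample size and with or without univariate selection, by the modest amounts shown above. Those amounts rest on assumed parameter counts and effect sizes; the half-widths rest on the article's 50% prevalence and an assumed c-index.

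The documents do not support calling the split invalid or biased, or treating 280/140 as settled. Lack of testing at a new site is a separate limitation, shared equally by the split and the bootstrap.

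**What to change.** Replace the split by the following.

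1. Build both models on all evaluable participants.
2. Estimate optimism-corrected c-index, R-squared and calibration slope by bootstrap with at least 500 resamples, repeating the univariate selection and any imputation in every resample.
3. Apply the estimated shrinkage to the coefficients.
4. As a secondary check for the web tool, add leave-one-institution-out (internal–external) validation. Where a region has only one institution, its residential-area coefficient cannot be estimated once that institution is left out, so use UV-B or latitude in place of that term in this check.

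The cost is a change of wording before the final analysis and more computing; no further recruitment is needed. The bootstrap estimate carries a small bias, about 0.01 to 0.02 in either direction in simulation, which should be acknowledged when the results are reported.
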